#### Intervention condition

Following randomization, participants in the intervention group receive access to the web-based training ‘InterAKTIV Sport’. Participants’ access to other exercise programmes (e.g. university sports programme, personal training) is not restricted. ‘InterAKTIV Sport’ consists of an introductory module, four main modules (1: motivation and objectives, 2: concrete planning, 3: barriers management, and 4: action control), and a final module (see Table 1). The components of the training are derived from the HAPA model.

**Table 1 Tab1:** Module of the web-based intervention ‘InterAKTIV Sport’

Module	Topic	Content
Intro	Introduction	- Information about the course of the training - Technical information
1	Motivation and objectives	- Formulating an exercise goal - Reflecting positive and negative consequences of the exercise goals - Intention formation
2	Action planning	- Concrete planning
3	Barrier management	- Identification of situative barriers - Development of strategies to cope with barriers
4	Action control	- Self-monitoring, self-evaluation, self-reinforcement - Coping with lapses into inactivity
Final	Completion	- Review of the intervention

Each module closes with a homework assignment encouraging the implementation of the new skills in daily life. New modules are available on a weekly basis, given that the participant has completed the previous chapter. The introduction and final module can be completed on the same day as the first or last content module. The training lasts for 3 weeks if a participant completes all modules within the recommended timeframe. To enhance adherence [36], participants are sent e-mail reminders after 3, 7, and 10 days when activated modules are not completed. In the last reminder, they are informed that their account will be deactivated within 4 days if they will not login again. Participants’ access to the intervention platform closes with sending the follow-up assessment.

The training was generated with the e-learning software Articulate Storyline 360. It is available on our own server with a pre-installed ILIAS application [37] which we use for enrolment and management of participants. Login on the platform takes place via personal access data and is open all the time. The usability of the intervention was tested in a pilot study [38]. Participants’ feedback resulted in an improved version of the intervention.

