#### Control condition

The control group receives the intervention after completing follow-up assessment. Control group participants are told that they will get access to the intervention after the follow-up assessment. No further instruction is given what to do—or not to do—during this time. Participants’ access to other exercise programmes (e.g. university sports programme, personal training) is not restricted. This is equivalent to “treatment as usual” (TAU) in medical efficacy studies. A detailed description of TAU is assessed at post-treatment. Figure 1 shows the study flow.

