### Statistical analyses

According to CONSORT statement [32], sample characteristics of both subgroups will be contrasted descriptively in order to detect relevant differences between the two samples. All analyses for the primary and secondary outcomes will be performed with an alpha level of 5% which means that the analyses for secondary analyses will be explorative. Outcome analyses will follow an intention-to-treat principle by including all randomized participants into the analyses. Outcomes will be analysed using a linear mixed model handling missing data under the assumption that data are missing at random. All participants and data points will be included in the mixed model analyses. The mixed model for the primary outcome (physical activity) will include group, time, and the interaction of group and time as fixed effects and participant and university as random effect. Analyses will use restricted maximum likelihood estimation (REML). For repeated measures (time), an autoregressive covariance structure with heterogeneous variances is assumed. Secondary outcomes will be analysed accordingly. We will calculate between-group effect sizes for the outcomes using the post-intervention estimated means and their pooled observed standard deviation. Additional per protocol analyses will include only those participants completing all three assessments (IG and CG) and at least three intervention modules (IG). For the main outcome, potential moderators will be analysed exploratively by including the following variables and all possible interactions in the mixed model: gender, body mass index, depressive symptoms, self-control competence and recruiting season (separate mixed model for each moderator). All analyses will be conducted using IBM SPSS.

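### The per-protocol set filters on module completion in the intervention arm only, so this additional contrast is not randomised and can lean towards the intervention

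*Protocol article*

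**What the plan says.** All references are to the protocol article.

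- **Main analysis (Statistical analyses).** "Outcome analyses will follow an intention-to-treat principle by including all randomized participants into the analyses". The mixed model for the primary outcome "will include group, time, and the interaction of group and time as fixed effects and participant and university as random effect". Between-group effect sizes are taken from the estimated post-intervention means, divided by a pooled observed standard deviation.
- **Per-protocol analysis (same section).** "Additional per protocol analyses will include only those participants" who meet the completion rule, which is to "include only those participants completing all three assessments (IG and CG) and at least three intervention modules (IG". That rule asks both arms for all three assessments and asks the intervention group alone for at least three modules. No caveat on interpretation is attached.
- **Modules (Intervention condition).** The training "consists of an introductory module, four main modules" and a final module, six units in all. "New modules are available on a weekly basis, given that the participant has completed the previous chapter". A participant who does not respond to reminders is told that "their account will be deactivated within 4 days if they will not login again". Platform access otherwise closes when the follow-up assessment is sent.
- **Controls (Control condition).** "The control group receives the intervention after completing follow-up assessment".

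**The concern.** Module completion is observed after randomisation and can be observed in one arm only. Because units open one after another and idle accounts are closed, reaching three of them selects people who keep going. On the trial's own theory (Background), planning, coping and action control are what turn an intention into exercise, and self-control competence is a listed moderator. It is therefore plausible that people who persist with modules also become or remain more active, whatever the training does. Removing the less persistent from one arm, without removing their counterparts from the other, then raises the intervention mean even under a true null.

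The rule also leaves three things loose:

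- It does not say whether the introduction counts. Read literally, the introduction plus main modules 1 and 2 qualifies, without barrier management or action control.
- It gives no time limit, so modules finished after t2 could qualify someone for the t2 comparison.
- It requires t3, so a participant with valid t2 data but no t3 is dropped from the t2 contrast.

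At stake is how a per-protocol effect size is read if it is published beside the intention-to-treat result without a warning.

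**Working it through.** **The plan's own figure.** The per-protocol rule carries no number. The nearest is the sample size (Proposed sample size): d = 0.5, two-sided 5%, 80% power. The normal approximation gives n = 2(1.960 + 0.842)²/0.5² = 62.8, so 63 per arm. The noncentral t gives 64 per arm, 128 in total, with power 80.1%. Then 128/(1 − 0.20) = 160. Both stated totals reproduce.

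**Inputs from the article.** 160 randomised 1:1, so 80 per arm; 80% completing assessments; the module filter in the intervention arm only; no control access before t3.

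**Inputs assumed, because the article does not give them.**
- q, the share of the intervention arm completing at least three modules: 80%, 65%, 50%, 35%.
- r, the correlation of persistence with the t2 outcome: 0 to 0.5.
- How closely assessment completion tracks module persistence: the same trait (correlation 1) or loosely related (0.5).

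**Closed form for the same-trait case.** If the top share p on a standard normal trait is kept, the mean of the kept group is m(p) = φ(z)/p, with z the (1 − p) quantile: m(0.8) = 0.350 and m(0.5) = 0.798. Controls are filtered too, at 80%, so

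spurious d = r × [m(q) − m(0.8)].

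For q = 0.5 this is 0.448r, or 0.13 at r = 0.3 and 0.22 at r = 0.5. For q = 0.8 it is zero at any r.

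**Simulation under a true null** (4,000 runs per cell, t-test on one t2 outcome). Cells show spurious d in outcome SD units, same trait / loosely related:

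| q | r = 0.1 | r = 0.2 | r = 0.3 | r = 0.5 |
|---|---|---|---|---|
| 80% | 0.00 / 0.02 | 0.00 / 0.04 | 0.00 / 0.07 | 0.00 / 0.12 |
| 65% | 0.03 / 0.04 | 0.05 / 0.08 | 0.06 / 0.13 | 0.11 / 0.22 |
| 50% | 0.05 / 0.06 | 0.09 / 0.13 | 0.14 / 0.20 | 0.23 / 0.33 |
| 35% | 0.08 / 0.09 | 0.14 / 0.18 | 0.21 / 0.27 | 0.36 / 0.45 |

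The simulation agrees with the closed form (q = 0.5: 0.138 and 0.229 simulated). With r = 0 the bias is zero and the two-sided error about 5%. For r up to 0.3 the error is at most about 21%. At r = 0.5 and q = 35% it is 37% (same trait) or 50% (loosely related).

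**Which r applies.** For the group-by-time test, r is the correlation of persistence with *change* in activity, because a stable difference is present at t1 and largely cancels. For an effect size from post-intervention means, r is the correlation with the *level* of activity. The listed fixed effects contain no baseline covariate, although Proposed sample size mentions baseline adjustment. Randomisation balances baseline in expectation in the full set, but not after the filter, so a stable difference passes straight into the per-protocol d.

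**The case against.** The strongest reply is that no main conclusion rests on this analysis: it is declared additional, and the main analysis keeps everyone randomised. That stands, and it limits the point to how a secondary result is read.

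Three stronger readings are tempting and are not supported.

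- *That persistent participants are compared with unselected controls.* Controls must also complete all three assessments. If module completers are essentially the assessment completers, the bias is about zero. Only the extra module condition is one-sided.
- *That the analysis will show an effect when there is none.* The bias has a direction but is not certain. Even the most extreme assumed cell gives false significance in about half of trials, and with r up to 0.3 in at most about a fifth.
- *That a per-protocol result near d = 0.5 would be largely selection.* The article takes 0.5 from earlier studies' per-protocol analyses and does not tie it to this completion rule. Values close to it appear only at the corner of the assumed range.

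Two further replies have some force. A threshold that the introduction plus two main modules can meet is lenient, which suggests higher retention and a smaller bias; this is one more reason to define what counts. A complier estimate also has its own assumption: completing fewer modules than the threshold must have no effect. Modules 1 and 2 cover motivation and action planning, so partial users may benefit, and the ratio would then overstate the complier effect. That does not rescue the per-protocol contrast, but it must be stated and tested.

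The cancellation of stable differences protects the group-by-time test to a large extent. It does not protect the effect size.

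**Conclusion.** The point holds in a limited form. The per-protocol rule puts a post-randomisation persistence filter on one arm, so its contrast is non-randomised and can be biased towards the intervention, most plainly in the effect size. Under a true null the spurious d is about 0 to 0.45 over the whole assumed range, and about 0.03 to 0.27 for r of 0.1 to 0.3 with 35% to 65% completing three modules. These figures rest on assumed r and q, on 80% assessment completion in both arms, and on a single t2 contrast in place of the full mixed model. They also assume that the stated effect-size method is applied to the per-protocol set, as nothing in the article says otherwise. The intention-to-treat result and the sample size arithmetic are untouched. The change is worth making because a randomisation-based alternative is available at little cost.

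**What to change.** Make the adherence analysis a complier average causal effect with randomisation as instrument. Control access is zero until t3, so non-compliance is one-sided and

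complier effect = intention-to-treat difference ÷ share of the intervention arm that is adherent.

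- **Numerator:** the intention-to-treat mixed-model estimate, adjusted for baseline IPAQ, with all randomised participants and the missing-at-random handling retained. Do not require t3 for the t2 contrast.
- **Denominator:** all participants randomised to the intervention, counting only main modules completed before the assessment being analysed.
- **Assumption:** state that no effect is assumed below the adherence threshold. Add a sensitivity analysis with a lower threshold, for example any main module completed.
- **If the existing per-protocol set is still reported:** adjust it for baseline IPAQ and label it non-randomised and descriptive.

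Under a true null the numerator is zero in expectation, so selection on persistence creates no effect at any r.

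The cost is precision and a little analysis work. Treating the adherent share as known, the confidence interval is the intention-to-treat interval multiplied by 1/q: 1.54 at q = 65%, 2.00 at 50%, 2.86 at 35%. The ratio adds essentially no test beyond intention to treat; it rescales the effect to adherent participants. No new data are needed, since the platform must already record completion in order to release the next module.

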## Discussion

Web-based interventions are a low-threshold, cost-effective way to disseminate physical activity among students. This study is the first high quality RCT to investigate the effect of a web-based physical activity intervention on amount of physical activity among students in Western countries. The implemented web-based intervention is based on the HAPA model of health behaviour change and targets psychological determinants of physical activity such as self-efficacy or action planning. We expect the intervention group to benefit from the web-based intervention with regard to physical activity, at post intervention and 3 months follow-up. In an exploratory approach, we also analyse motivational and volitional determinants of exercise, quality of life and depressive symptoms. The results of this study will be of great relevance for student health campaigns, as they reflect the effectiveness of a self-help intervention for young adults seeking support in establishing a healthy lifestyle.

From a lifespan perspective, it is important to help students find their way into regular physical activity [53]. A special characteristic of the intervention is the focus on exercise behaviour. For our participants, the intervention does not explicitly target health or health behaviour, but rather frames exercise as an activity full of pleasure, vividness and social experience. By activating motives that are relevant for younger adults, the intervention aims at activating the participants without expatiating a health perspective. As Kazdin and Blase [54] point out, innovative approaches are needed to decrease the global burden of diseases.

This study is a high quality RCT with three assessment points and intention-to-treat analysis meeting the state-of-the-art of randomized controlled studies [32]. Recruitment covers almost 20 universities in three countries, leading to high external validity of the results. The intervention is theory-based and was improved after a pilot study. Yet, the study has limitations that deserve note. The inclusion criterion concerning exercise at baseline is set at 0–2 times of exercise per week. It may be that the intervention effectiveness varies between no- und low-exercisers. We use validated scales and items that have been used in former studies. However, validation studies did not particularly focus on young adults. All outcome measures were based on self-reports only. Self-reports underlie potential biases such as social desirability or memory effects. Objective measures of physical activity were not implemented considering the organizational effort and the resources available. A replication study using objective measures would be beneficial. As the study is too underpowered to properly analyse potential moderating variables, the moderator analyses are explorative.

With regard to the intervention, we do not provide any guidance in terms of content for the intervention participants [55]. This may restrict the range of effectiveness of our physical activity interventions. Last, the recruitment of participants has started before submitting the study protocol. However, the study has been registered before the beginning of recruitment and no changes have been made to the registry.

### Trial status

Protocol version number: 1 (November 18, 2019)

First day of recruitment: March 13, 2019

Expected end of recruitment: October 30, 2020

## Data Availability

Not applicable

## Abbreviations

BSA: Bewegungs- und Sportaktivitätsfragebogen (German acronym for Physical Activity, Exercise, and Sport Questionnaire)
CES-D: Center for Epidemiologic Studies Depression Scale
CG: Control group
HAPA: Health Action Process Approach
IG: Intervention group
RCT: Randomized-controlled trial
VCQ: Volitional Components Questionnaire
WHOQOL-BREF: World Health Organization Quality of Life Scale, short version
